### Data management

A Trial Steering Committee (TSC) has been established to oversee study conduct. The TSC comprises an independent chairperson (surgeon) and 3 other independent members (surgeon, statistician, and patient representative). The TSC have established formal terms of reference detailing its responsibilities and operational procedures.

An independent Data Monitoring Committee (DMC) has been established to review safety data, provide guidance on interim analyses and is advisory to the TSC. The DMC consists of a chairperson (statistician) and 3 other members (2 academic surgeons and 1 statistician) who are unblinded to participant treatment groups. Their duties and operational framework are described by terms of reference, defined from the DMC charter [22]. All members of the TSC, DMC, and the trial statistician are independent from the sponsor.

Both the TSC and DMC will hold a joint meeting before recruitment begins and will continue to convene every 6 months after recruitment has commenced. The DMC has the power to recommend continuation or termination of the study based on the evaluation of unblinded results.

### Integrity of data collection

Designated members of the research team will be responsible for data entry at different steps of the patient pathway. All researchers are trained to ensure the accuracy of the relevant outcome and will ensure that entries can be verified by the source data. Data will be collected pseudonymously and managed using Research Electronic Data Capture (REDCap) hosted by University College London (UCL). REDCap is a secure web-based software platform designed to support data capture for research studies on bespoke electronic case report forms (eCRFs). Unblinded research staff will deal with randomisation and per protocol operating, whereas blinded research staff will collect baseline information and primary and secondary outcome data.

### Audit procedures

The sponsor has confirmed Capacity and Capability to undertake the trial in line with Health Research Authority (HRA) guidance. This included an audit of site file documents including Good Clinical Practice (GCP) certificates and training records [23]. The sponsor will notify the Principal Investigator in advance if further internal audits are planned, typically at the halfway point and at study close.

### Protocol amendments

Substantial amendments require reporting to the REC in line with Health Research Authority guidance. Non-substantial amendments will be deliberated by the TSC and if deemed acceptable, notification will be provided to the Sponsor.

### Adverse event reporting

In this trial, adverse events (AE) are defined as any untoward medical occurrence in a subject to whom an intervention has been administered, including occurrences which are not necessarily caused by or related to the intervention and that exceed grade 1 of the Clavien-Dindo classification [24]. Serious adverse events (SAE) are defined as events which result in death, are life-threatening, require or prolong hospitalisation, or result in significant disability/incapacity. However, the following exceptions are already defined in this protocol and so will not be recorded as an adverse event; these are trocar-site hernia which will be assessed as a primary outcome, and wound events defined under SSO will be assessed as a secondary outcome.

We do not anticipate any device-specific AEs or SAEs. Suture granuloma and chronic draining sinuses are theoretically more common with non-absorbable suture material, but the largest published series of Duramesh implantation suggests these are rare, with an incidence of 0% and 0.3%, respectively [25]. Both will be reported as secondary outcomes, as stated above. AEs and SAEs will be reported unsolicited, and their relationship to the treatment arm graded as either unrelated, possible, probable or causal. Patients admitted to the hospital after their operation are reviewed daily by blinded outcome assessors for AEs, SAEs and wound events. Following discharge, trial participants are asked to inform the trial coordinator if they re-present to the hospital, whether that be related or unrelated to the index operation. Participants are also asked to contact the trial coordinator if they have any health-related concern so that AEs or SAEs are not missed.

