### Primary outcome

The primary endpoint is the cumulative occurrence of trocar-site hernia (TSH) over 2 years following the index operation. For this trial, TSH is defined as an ultrasound-detected fascial defect of 10 mm or greater within the vicinity of the periumbilical scar, with or without protrusion of intraabdominal or pre-peritoneal contents, and with or without symptoms.

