### Secondary outcomes

These include:Incidence of periumbilical surgical site infection (SSI) within 90 days, categorised by the Centers for Disease Control and Prevention (CDC) [14] as superficial, deep and organ-space.Incidence of periumbilical surgical site occurrence (SSO) within 90 days, categorised by the Ventral Hernia Working Group (VHWG) [15] as SSI, seroma, haematoma, superficial dehiscence, fascial dehiscence, enterocutaneous fistula, suture granuloma and chronic sinus tract.Reoperation within 90 days of the index operation.Length of hospital stay.Mortality within 90 days of the index operation.Measurement of postoperative quality of life (QoL) using modified versions of validated questionnaires – EuraHS-QoL score [16] and Carolinas Comfort Scale (CCS) [17, 18].

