### One-year and 2-year follow-up

Data collected at these timepoints are QoL scores and presence of TSH. Ultrasound examination will be performed by the same sonographers who remain blinded to the participant treatment arm. Patients with confirmed TSH detected before the primary endpoint of 2 years are offered ongoing follow-up to monitor TSH size and continued QoL assessment.

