### Progression criteria

The internal pilot analysis will present total participants recruited, monthly recruitment rates and available secondary outcome data. Criteria for trial progression are outlined in Table 2. If all criteria are green, the trial will continue without protocol modification; if one or more criteria are amber, adaptations may be proposed to address the shortfall; one or more red criteria will require discussion about whether ongoing participant recruitment is feasible.

**Table 2 Tab2:** Progression criteria stipulated at the interim analysis at 6 months

Criterion	Target	Green	Amber	Red
Participant recruitment	84	≥ 60	35–59	< 34
Randomisation rate (minimum number recruited per month)	14	≥ 9	5–8	< 5
Secondary outcome data available	80%	≥ 70%	50–70%	< 50%

In addition to recruitment analysis, the DMC will examine the unblinded frequency and severity of adverse events. If serious adverse events occur during the internal pilot that are assessed to be directly related to Duramesh and/or are disproportionately associated with Duramesh compared to conventional suture, then the DMC has the option to recommend trial termination. No specific number is declared, but judgement will be based on the severity of harm and its frequency relative to conventional suture.

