## Discussion

Trocar-site hernia (TSH) is a clinically important complication after laparoscopic surgery, with potential sequelae of pain and bowel incarceration. The TROCAR trial evaluates the comparative effectiveness of Duramesh versus conventional suture (J-Vicryl or J-PDS) for reducing the incidence of trocar-site hernia at periumbilical trocar sites. The hypothesis is that Duramesh is superior to conventional suture.

The mechanism of action of Duramesh is by distributing tension at the suture–tissue interface and by promoting fibrovascular integration between its polypropylene filaments [11]. This theoretically reduces fascial tearing and subsequent hernia formation. Preclinical studies in animal models have shown greater resistance to suture pull-through and greater ultimate tensile strength before tearing [12, 26]. Our team performed a systematic review of clinical studies [13] which suggested Duramesh may be associated with low rates of incisional hernia, but the available evidence remains limited by study quality and high risk of bias. Randomised controlled trials (RCTs) are therefore needed before widespread adoption can be recommended.

The INDURATE trial, currently recruiting in Madrid [27], also investigates Duramesh closure for periumbilical trocar-sites. However, its design includes certain constraints, including the absence of blinded outcome assessment, relatively short follow-up duration (1 year), and the assumption of large absolute risk reduction for power calculation (20%). This results in a small sample size of 124 participants after accounting for a 5% rate of loss to follow up. Other RCTs are also currently recruiting, but these investigate Duramesh closure of laparotomy and ileostomy wounds [28, 29] and are not designed with patient or outcome assessor blinding. TROCAR therefore complements ongoing research and is positioned to be the first double-blind and adequately powered trial for TSH.

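### Trocar-site hernia is exempt from adverse event recording with no seriousness limit, so, read literally, no listed safety or outcome measure shows that a hernia became serious after day 90

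*Protocol article*

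**What the plan says.** All references are to the protocol article.

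- **Adverse event reporting** defines serious adverse events as "events which result in death, are life-threatening, require or prolong hospitalisation, or result in significant disability/incapacity". The next sentence makes exceptions that "will not be recorded as an adverse event; these are trocar-site hernia which will be assessed as a primary outcome". It also exempts wound events, because "wound events defined under SSO will be assessed as a secondary outcome"; that second exemption is not at issue here.
- **Primary outcome** counts an ultrasound-detected defect of at least 10 mm over 2 years, "with or without protrusion of intraabdominal or pre-peritoneal contents, and with or without symptoms".
- **Secondary outcomes** include "Reoperation within 90 days of the index operation" and mortality over the same window. **Three-month follow-up** collects readmission and return to theatre, also to 90 days.
- **One-year and 2-year follow-up** states: "Data collected at these timepoints are QoL scores and presence of TSH". A hernia confirmed before 2 years is followed for size and quality of life.
- **Discussion** calls trocar-site hernia clinically important, "with potential sequelae of pain and bowel incarceration".
- **Data management** describes a DMC that is unblinded, reviews safety data and meets every 6 months.

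**The concern.** Leaving an efficacy endpoint out of adverse event reporting is sensible when the endpoint carries the information that the safety record would have carried. Here it does not. The primary outcome is yes or no, so a silent 10 mm gap and a hernia that ends in an emergency admission score the same. The outcomes that could separate them end at day 90, while hernias are counted for 2 years.

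Two things are at stake. First, the DMC could be reviewing serious adverse events from which the most relevant late harm has been removed by rule. Under Protocol deviations, failing to report a serious adverse event to the ethics committee within 14 days is a major deviation; an exempt event would not start that clock. Second, the Discussion accepts that the relevance of an occult hernia is debatable. Serious hernia events by arm bear directly on that question, and the literal rule keeps them out of the tables.

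**Working it through.** **The plan's own figure.** With 25% versus 10%, two-sided 5% significance, 80% power and 1:1 allocation:

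n per arm = [1.960 × √(2 × 0.175 × 0.825) + 0.842 × √(0.25 × 0.75 + 0.10 × 0.90)]² / 0.15² = 99.5, rounded up to 100.

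Allowing for 20% loss: 200 / (1 − 0.20) = 250. Both stated figures reproduce, and nothing in this point disturbs them.

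**Where would a serious hernia event be recorded?**

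| Record | Up to day 90 | After day 90 |
|---|---|---|
| Primary outcome | Hernia yes/no | Hernia yes/no |
| Scan detail | Defect size, sac size, content | Size followed if a hernia is confirmed |
| Quality of life | 3 months | 1 and 2 years |
| Reoperation, readmission, mortality | Yes | Not listed |
| Adverse event record | Exempt, read literally | Exempt, read literally |

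The last two rows are where hospitalisation, a life-threatening event or death would appear. After day 90 neither is available on the literal reading. The 90-day windows cover 90/730 = 12.3% of the 2-year follow-up. That is a share of time, not of events.

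**How many hernias does the exemption cover, on the plan's rates?**

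- 200 evaluable: 100 × 0.25 + 100 × 0.10 = 25 + 10 = 35.
- All 250 evaluable: 125 × 0.25 + 125 × 0.10 = 31.25 + 12.5 = 43.75, about 44.

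**How many could be serious?** The documents give no rate, so the proportion f is an assumption, taken from 1% to 20%.

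| f | 35 hernias | 43.75 hernias |
|---|---|---|
| 1% | 0.35 | 0.44 |
| 20% | 7.0 | 8.75 |

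The range is about 0.4 to 9 events over 2 years. Some would fall before day 90 and be visible through the 90-day outcomes, so the number affected is smaller by an amount that the documents do not allow one to calculate. With 35 hernias, the chance of at least one serious event is 1 − (1 − f)^35: about 30% at f = 1% and 97% at f = 10%.

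**The case against.** Much can fairly be said for the plan.

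- **The hernia is not lost.** A reader might infer that a serious hernia after day 90 appears in no table at all. The documents do not support that: if ultrasound shows a qualifying defect, it is counted by arm in the primary outcome. What is missing is its seriousness. A hernia operated on as an emergency before any trial scan might miss the ultrasound-based outcome as well, but the text does not settle this.
- **Complications may not be exempt.** The exception names the hernia, which Primary outcome defines as a fascial defect. Bowel obstruction, an emergency admission or a death could be read as separate occurrences that remain reportable. Participants are also asked to tell the coordinator of any return to hospital, with no time limit, so the event can become known. This reading is available but not stated. The exception follows the serious adverse event definition directly and carries no limit, so two members of staff could classify the same admission differently.
- **Some severity is recorded.** Scans record size and content, and quality of life is measured at 1 and 2 years. These are useful but do not show admission, emergency surgery or death.
- **The pilot stopping provision is not the main problem.** It reads "If serious adverse events occur during the internal pilot that are assessed to be directly related to Duramesh" and so covers the 6-month pilot, when no participant can be more than about three months past day 90. The argument rests on the DMC's continuing review instead.
- **The article condenses a fuller protocol, and Table 1 is not shown.** Either may list further data, and the follow-up section does not say that its list is exhaustive. But the exemption is a stated rule, not an omitted detail, so the condensed format does not by itself answer the point.

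**Conclusion.** The point holds in limited form. As worded, the rule exempts trocar-site hernia from adverse event recording whatever its seriousness, on a justification that works for occult defects but not for serious events. After day 90, no listed outcome shows that a hernia led to hospitalisation, a life-threatening event, disability or death. Whether such consequences are themselves exempt is ambiguous, and that ambiguity is reason enough to amend the sentence.

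The size is modest: about 0.4 to 9 serious events, resting on the plan's 25% and 10% rates, on 200 to 250 evaluable participants, and on an assumed 1% to 20% that has no source in the documents. So few events would support description by arm, not a formal comparison. They would still matter to a DMC which, under Progression criteria, weighs severity and relative frequency without a fixed number. The sample size, the primary endpoint and its analysis are unaffected. This is an inexpensive improvement to safety recording.

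**What to change.** In Adverse event reporting:

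1. Limit the exemption to trocar-site hernia that does not meet the protocol's own serious adverse event definition, such as a defect found only at a scheduled scan.
2. State that hernia events meeting that definition are recorded as serious adverse events through 2 years.
3. Include them in the unblinded safety data given to the DMC at its 6-monthly meetings, and tabulate them descriptively by arm with the other safety data.
4. State that the hernia still counts in the primary outcome.

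This changes recording only. Participants are already asked to report returns to hospital, so no new visit, test or staff is needed. The cost is a sentence or two in the protocol, a line in the DMC report, a few more serious adverse event forms, and the same hernia appearing in both the efficacy and safety tables, which a footnote can explain.

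### Wound events are exempt from AE/SAE recording without limit of time or seriousness, but the outcome that replaces that recording ends at day 90

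*Protocol article*

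**What the plan says.** Four parts of the protocol article bear on this.

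- **Adverse event reporting.** After defining AEs (above Clavien-Dindo grade 1) and SAEs, the section states that "the following exceptions are already defined in this protocol and so will not be recorded as an adverse event". The exceptions are trocar-site hernia and SSO, of which it says "wound events defined under SSO will be assessed as a secondary outcome". It also says that granuloma and chronic sinus are in theory more frequent with material that does not absorb, and sends both to the secondary outcomes.
- **Secondary outcomes.** The measure is "Incidence of periumbilical surgical site occurrence (SSO) within 90 days". Its categories include SSI, seroma, haematoma and "superficial dehiscence, fascial dehiscence, enterocutaneous fistula, suture granuloma and chronic sinus tract". Return to theatre has the same window: "Reoperation within 90 days of the index operation". The three-month follow-up section collects SSO and return to theatre to day 90.
- **One-year and 2-year follow-up.** "Data collected at these timepoints are QoL scores and presence of TSH".
- **Progression criteria.** The DMC examines unblinded adverse events. Its option to recommend termination begins "If serious adverse events occur during the internal pilot that are assessed to be directly related to Duramesh", and also covers SAEs that are disproportionate in the Duramesh arm.

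**The concern.** The exemption assumes that every exempted event is recorded somewhere else. For trocar-site hernia this is true, because the primary outcome runs for the full 2 years. For SSO it is true only to day 90.

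The exemption also comes directly after the SAE definition and does not bring serious events back in. An SSO that leads to readmission is handled only as an outcome. It then carries no SAE reporting duty, although the protocol deviations section treats failure to report an SAE to the ethics committee within 14 days as a major deviation.

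At stake is the comparison of harms. The device is permanent, the protocol itself names granuloma and sinus as plausible consequences of such material, and its benefit is assessed over 2 years. If wound harm is sought systematically for only 90 days, the 2-year account of benefit and harm is uneven. The primary analysis is not affected.

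**Working it through.** The protocol gives no figure of its own for this point, so the check is mainly a comparison of sections, followed by arithmetic on the likely number of events.

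**1. A serious SSO before day 90** (for example a deep SSI needing readmission)
- It meets the SAE definition, which includes events that lead to or lengthen a hospital stay.
- It is also an SSO, so the exemption says that it is not recorded as an AE. It is therefore not an SAE.
- It is still collected: SSI by depth, SSO by category, readmission and return to theatre are all recorded at three months.
- In the progression criteria, the unblinded review and the termination option are worded in terms of AEs and SAEs. Taken literally, neither counts this event. The pilot report does present available secondary outcome data, so the event can be seen there.

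**2. An SSO after day 90** (for example a chronic sinus or granuloma)
- It is outside the secondary outcome, which stops at day 90.
- It is not among the items listed for the 1- and 2-year visits.
- Whether it is an AE depends on how the exemption is read:
  - *By event type:* it stays exempt and no recording route is stated. The neighbouring exemption, for trocar-site hernia, holds throughout follow-up, which favours this reading.
  - *By outcome:* the exemption lapses once the event is no longer assessed as a secondary outcome. The event is then an AE if it exceeds Clavien-Dindo grade 1, and it reaches the trial through unsolicited reporting. Grade 1 events are not recorded on either reading.

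**3. Likely number of events**
- Inputs: 250 participants allocated 1:1, so 250 / 2 = 125 on Duramesh. The cited series gives 0% granuloma and 0.3% chronic sinus (adverse event reporting section). Rates of 1% and 3% are assumptions that show the range.
- Expected events = 125 × p. Chance of at least one = 1 − (1 − p)^125.

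| p | Expected events | Chance of at least one |
|---|---|---|
| 0.3% (cited) | 0.375 | 31% |
| 1% (assumed) | 1.25 | 72% |
| 3% (assumed) | 3.75 | 98% |

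These are total events over whatever follow-up the rate refers to. The documents do not say what share falls after day 90.

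**4. What the pilot review could see of late events**
- Assume that 84 patients accrue evenly over 6 months (182.6 days). Patients past day 90 at the end = 84 × (182.6 − 90) / 182.6 ≈ 43.
- Their time after day 90 = (84 / 182.6) × (92.6² / 2) / 30.44 ≈ 65 person-months.
- With 250 patients followed to 2 years without loss, time after day 90 = 250 × 640.5 / 30.44 ≈ 5,260 person-months.
- The pilot therefore holds about 1% of the late observation time (65 / 5,260). Late events have to be captured by the later visits.

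**The case against.** A reader might infer that late wound events and device removal are captured nowhere and that the DMC cannot see serious wound events. The documents do not support that.

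- **Late events may return to AE recording.** The exemption can fairly be read as tied to the 90-day outcome. Participants are also asked, with no end date, to report any return to hospital and any worry about their health. This stands, and it makes the gap an ambiguity rather than a proven total loss. It does not replace asking at a scheduled visit.
- **Explant and wound reoperation are not SSO categories.** They are not exempt by name. The protocol deviations section covers device-related reoperation and explant without a time limit, and a case needing admission fits the SAE definition. This stands. What remains is that the reoperation outcome ends at day 90.
- **The DMC has wider powers.** Under data management it reviews safety data, is unblinded, meets every 6 months and may recommend termination on unblinded results. No numerical trigger is set, and termination rules authorised in May 2025 are not shown. This stands: the defect is in the stated wording, not in the DMC's access to data.
- **Calendar time is not events.** Days 91 to 730 are 640 of 730 days, or 88%, but this does not mean that 88% of events are missed. The documents do not say that granuloma or sinus occur late.
- **Some material is not shown.** Table 1, which covers unscheduled visits, and the full protocol might hold wound fields. Such fields would narrow the collection gap, but would not by themselves change the exemption or the 90-day outcome windows stated in the article.

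**Conclusion.** The point holds in limited form. The stated recording rule exempts SSO without regard to time or seriousness, while the outcome that justifies the exemption ends at day 90. Serious SSO are therefore, as written, not SAEs and lie outside the SAE wording of the DMC's termination option, though they are collected and can be seen as outcomes. SSO after day 90 have no scheduled collection in the text and depend at best on unsolicited reports above Clavien-Dindo grade 1.

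The effect is a possible under-count of late wound harm. It is probably small in number: about 0.4 sinuses in 125 patients at the cited rate, and 1.3 to 3.8 at assumed rates of 1% to 3%. With so few events, each missed one weighs on the comparison of harms. The documents do not establish that the 2-year benefit-risk conclusion would be biased, only that it could rest on incomplete harm data.

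This should be fixed. Confidence is moderate, because it depends on how the exemption is read and on a visit table that is not shown.

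**What to change.** Reconcile the sections on secondary outcomes, one-year and 2-year follow-up, adverse event reporting and progression criteria.

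1. **Adverse event reporting:** limit the exemption to non-serious SSO within 90 days. Any SSO that meets the SAE definition, and any SSO after day 90, is recorded under AE/SAE reporting.
2. **One-year and 2-year follow-up:** ask about SSO and wound reoperation since the last visit, and report both by arm.
3. **Progression criteria:** word the DMC's safety review and termination option so that they cover serious SSO as well as SAEs.

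The cost is a few eCRF fields at visits that already take place, slightly more SAE reporting and a protocol amendment. Recruitment began in June 2025, so the first 1-year visits fall around June 2026. An amendment in force by then would cover every late visit.

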### Participant timeline (Table 1) and baseline data

**Table 1 Tab1:**
[figure not shown]
Scheduled and unscheduled visits with timepoints for data collection

Data will be recorded using electronic case report forms (eCRFs) on a secure web-based system (Project REDCap, Vanderbilt University, TN, USA). These consist of baseline demographics, medical history, treatment group, operative details, and primary and secondary outcomes. Follow-up timepoints are 3 months, 1 year and 2 years after the index operation. Additionally, patients requiring inpatient admission will be reviewed by a researcher before discharge for wound events as defined previously.

Baseline demographic data includes age, gender, smoking status, and previous abdominal surgery. Medical history includes history of diabetes, active malignancy, medications affecting healing (chemotherapy, steroids, biologics), ASA grade and comorbidities. Operative details include responsible consultant, pre-operative antibiotics, laparoscopic operation, length of procedure, CDC wound classification, and material used for skin closure.

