### Three-month follow-up

Participants are contacted by telephone to arrange a suitable time to visit the outpatient clinic. Information gathered will include length of hospital stay, readmissions within 90 days, return to theatre within 90 days, SSO within 90 days and QoL using modified versions of validated questionnaires. Furthermore, participants will have physical and ultrasound examinations performed by a trained sonographer for the presence of TSH. In this trial, imaging is the definitive modality for detecting the primary outcome. The precise extent (in mm) of any defect, if present, will be recorded, as will whether there is any hernia through this. If so, the width and craniocaudal diameter of the hernia sac will be recorded, along with the presence of any content beyond fat.

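### Adverse events after 90 days rest on unsolicited reports, although every participant is due to be seen at 1 and 2 years, so late harm is likely to be under-counted in both arms

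*Protocol article*

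**What the plan says.** Under Adverse event reporting, the article sets the mode of collection: "AEs and SAEs will be reported unsolicited". It then describes two phases.

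- **In hospital**, capture is active: "Patients admitted to the hospital after their operation are reviewed daily by blinded outcome assessors for AEs, SAEs and wound events".
- **After discharge**, it passes to the participant: "trial participants are asked to inform the trial coordinator if they re-present to the hospital", and "Participants are also asked to contact the trial coordinator if they have any health-related concern so that AEs or SAEs are not missed".

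Contact is nevertheless scheduled: "Follow-up timepoints are 3 months, 1 year and 2 years after the index operation" (Participant timeline and baseline data). The Three-month follow-up section lists, among other items, "readmissions within 90 days, return to theatre within 90 days, SSO within 90 days and QoL". For the later visits, One-year and 2-year follow-up says: "Data collected at these timepoints are QoL scores and presence of TSH".

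Adverse events are defined broadly. They include events unrelated to the intervention, provided they exceed Clavien-Dindo grade 1, and any event requiring hospitalisation is serious. Trocar-site hernia and wound events classed as surgical site occurrences are exempt from adverse-event recording. This point concerns the events that remain reportable.

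**The concern.** The article relies on self-report to make sure that nothing is missed, yet it has appointments at which every attender could be asked. From day 91 onward, no stated visit item asks about admissions, operations or new health problems. A late admission for obstruction, or treatment at another hospital, reaches the trial only if the participant thinks to call.

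The timing matters because of the comparison being made. Duramesh consists of polypropylene filaments (Discussion), and the adverse-event section itself discusses it as non-absorbable. The control is a slowly absorbable suture (Study design). Late follow-up is when a permanent material could show harm that an absorbed one would not.

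Two uses of the data are at stake. The Data Monitoring Committee meets every 6 months and may recommend termination on unblinded results (Data management), and the final safety data are to be reported descriptively (Publication policy). Both need reasonably complete counts. The protocol also treats failure to report a serious adverse event to the ethics committee within 14 days as a major deviation, and an event that the team never hears of cannot be reported.

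**Working it through.** **1. Stated capture, period by period**

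| Period | Stated route for reportable events |
|---|---|
| Inpatient stay | Daily review by blinded assessors |
| Discharge to day 90 | Self-report, plus the 3-month enquiry on readmission, return to theatre and surgical site occurrences |
| Day 91 to 2 years | Self-report only; the 1- and 2-year visits list quality of life and hernia |

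The last row covers (730 − 90) / 730 = 88% of the follow-up time.

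**2. Inputs for an illustration**

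From the article: 250 randomised 1:1, so 125 per arm; 20% loss to follow-up, so 100 per arm at 2 years. The article gives no late event rate and no capture rate, so the true rate p and the captured share c below are assumptions.

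**3. Chance that no event is recorded in the Duramesh arm**

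P(none) = (1 − p × c)^N.

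For p = 2%, N = 125:
- full capture: 0.98^125 = 8% (expected count 125 × 0.02 = 2.5)
- half capture: 0.99^125 = 28% (expected count 1.25)

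Across a range of assumptions:

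| True rate | N | c = 100% | c = 50% | c = 30% |
|---|---|---|---|---|
| 1% | 125 | 28% | 53% | 69% |
| 2% | 125 | 8% | 28% | 47% |
| 3% | 125 | 2% | 15% | 32% |
| 2% | 100 | 13% | 37% | 55% |

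**4. Effect on the comparison when capture is equal in both arms**

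The risk ratio is unchanged, because c cancels. The risk difference shrinks in proportion to c: for an assumed 5% v 1%, it falls from 4.0 points to 0.5 × 4.0 = 2.0 points at half capture.

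For an assumed 8% v 2% with 125 per arm, full enumeration of the two-sided Fisher exact test at 5% gives a chance of separating the arms of 48% at full capture, 30% at 70% capture and 16% at half capture. The article plans no such test, so these figures only describe the loss of sensitivity.

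**5. Which committee decision is affected**

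The Progression criteria section says of the pilot safety review that "judgement will be based on the severity of harm and its frequency relative to conventional suture". That review concerns serious events during a 6-month internal pilot. No participant can have reached a 1-year visit by then, so the missing questions at 1 and 2 years cannot bear on it. The committee's later six-monthly reviews and the final report are the places affected.

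**The case against.** **Capture is not wholly passive.** Inpatients are reviewed daily, and major early harm is asked about at 3 months. This stands, and it confines the gap chiefly to the time after 90 days.

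**The article is a condensed text.** Table 1, the visit schedule, is not shown, and the full protocol may list an adverse-event check at each visit. That is a fair caution. However, the point rests on two positive statements, that events are unsolicited and what the late visits collect. If Table 1 does hold such a check, it conflicts with both, and the text still needs correcting.

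**Symptoms are partly covered.** The modified EuraHS-QoL and Carolinas Comfort Scale are completed at all three visits and address the umbilical region, so persistent local discomfort does not depend wholly on a telephone call. This also stands, but a quality-of-life score does not record an admission or an operation.

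**Does passive reporting make Duramesh look safer?** A reader might infer this, because participants with an early detected hernia are offered ongoing follow-up and more hernias are expected in the control arm (25% v 10%). The documents do not support it. Participants and outcome assessors are blinded and both arms share one reporting route, so equal under-counting is the default expectation. The ongoing follow-up is described as monitoring hernia size and quality of life. It is not said to add visits before 2 years, nor to include adverse-event questions.

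**Small numbers limit the safety comparison in any case.** True: even with full capture, the assumed 8% v 2% is separated less than half the time. That is a reason not to lose further events when the remedy is cheap.

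**Conclusion.** The concern holds in a limited form. As the article is worded, reportable adverse events and serious adverse events between day 91 and 2 years depend on participants volunteering them, and under-counting in both arms is the likely result. Bias between the arms is possible but not shown. The primary outcome, the sample size and the pilot decision are not affected.

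The size cannot be fixed from the documents. On the assumption of a 2% event rate among 125 Duramesh patients, moving from full to half capture raises the chance of seeing no event from 8% to 28%. Both the rate and the capture share are assumed. The conclusion also assumes that the unseen visit schedule does not already provide for the enquiry.

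**What to change.** Replace the statement that "AEs and SAEs will be reported unsolicited" with a fixed enquiry. At the 3-month, 1-year and 2-year visits, the blinded assessor asks every participant in both arms, in the same words, about any hospital attendance, operation or new health problem since last contact. The answer, including 'none', is entered in the eCRF. At 3 months the question covers events other than those already gathered there. Keep participant-initiated reports between visits, since a visit question completes the count but does not make reporting prompt. Bring Table 1 and the One-year and 2-year follow-up section into line.

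The cost is one eCRF page, a few minutes at visits that already exist, and more minor events to classify. No visit, treatment, blinding arrangement or sample size changes. Recruitment began in June 2025, so the first 1-year visits fall around June 2026; a change made before then would cover all of the late visits.
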